## Abstract

**Background::**

Around 90% of sciatica cases are due to a herniated intervertebral disc in the lumbar region. Ankle acupuncture (AA) has been reported to be effective in the treatment of acute nonspecific low back pain. This study aims to evaluate the efficacy of a single session of ankle acupuncture for disc-related sciatica.

**Method::**

This will be a double-blinded, randomized controlled clinical trial. Patients diagnosed with disc-related sciatica will be randomly divided into 3 parallel groups. The treatment group (n = 30) will receive ankle acupuncture. The 2 control groups will either undergo traditional needle manipulation (n = 30) or sham acupuncture (n = 30) at the same point as the treatment group. The primary outcome will be pain intensity on a visual analog scale (VAS). The secondary outcomes will be paresthesia intensity on a VAS and the Abbreviated Acceptability Rating Profile (AAPR). The success of blinding will be evaluated, and the needle-induced sensation and adverse events will be recorded. All outcomes will be evaluated before, during, and after the treatment.

**Discussion::**

This study will determine the immediate effect and specificity of ankle acupuncture for the treatment of disc-related sciatica. We anticipate that ankle acupuncture might be more effective than traditional needle manipulation or sham acupuncture.

**Trial registration:**

ChiCTR-IPR-15007127 (http://www.chictr.org.cn/showprojen.aspx?proj=11989)

## Introduction

1

Sciatica is characterized by sciatic nerve pain (pain that radiates from the low back to below the knee), paresthesia (mostly numbness and tingling), and muscle weakness in the affected leg or foot.^[2]^ These symptoms can lead to motor disabilities^[1]^ and mental disorders such as depression and anxiety.^[3]^ The prevalence of sciatica ranges from 1.2% to 43%.^[4]^ The most common cause of sciatica is herniation of the nucleus pulposus. Indeed, about 90% of sciatica cases are due to a herniated disc involving nerve root compression. Other possible causes include a narrow lumbar canal, foraminal stenosis, tumors, and cysts.^[5]^ Herniated lumbar disc-related sciatica is one of the most common conditions managed in primary medical care and a significant cause of absence from work and early retirement. Patients, families, and the society at large all carry part of the burden.^[6]^

Sciatica resolves without treatment in the majority of cases. However, many patients endure substantial pain and disability.^[7,8]^ Medication and physical therapy are used as the initial treatment options for pain control. However, there is little evidence for the efficacy of pain medication.^[9]^ Several systematic reviews have analyzed the efficacy and safety of various drugs such as opioids and steroids, but the validity of the studies is limited.^[10–12]^ Furthermore, the use of pain medication has been associated with adverse effects such as sedation, dizziness, ataxia, and nausea.^[13]^ Similarly, there is little evidence for the efficacy of invasive surgeries such as lumbar discectomy and epidural steroid injections (ESIs).^[8,14,15]^

Acupuncture and electroacupuncture (EA) have been applied for the treatment of sciatica since the early 1990s,^[16–18]^ but results of studies on their efficacy have been inconsistent. According to the theory of Traditional Chinese Medicine (TCM), acupuncture needles are inserted into the body, and sufficient manual needling manipulation (e.g., lifting-thrusting and twisting-rotating) of the inserted needles elicits a composite of sensations (the response of the characteristic needle-manipulation sensation is termed *deqi*, which generally manifests as numbness, heaviness, distention, and soreness), which is believed to be an indispensable component in achieving a therapeutic effect. It is noteworthy that in clinical practice, many patients are afraid of the *deqi* sensation. Fear of needle-manipulation sensation is an important reason as to why patients choose to forego acupuncture treatment.

Ankle acupuncture (AA) is a type of subcutaneous acupuncture that has been developed in the 1970s.^[19]^ Compared with traditional acupuncture manipulation, AA penetrates the skin and inserts the needles shallowly in the subcutaneous tissue above the ankle, with no characteristic needle-manipulation sensation. Patients are more likely to accept AA due to the absence of needle-manipulation sensation. In addition, as it requires only the insertion of a single needle with no further manual manipulation, it can be easily taught to medical staff without much knowledge about acupuncture. Accumulating evidence from Chinese literature sources reveals that AA has similar therapeutic effects as traditional acupuncture in the treatment of pain.^[20]^ Some studies have reported the efficacy of AA for the treatment of sciatica.^[21,22]^ However, these studies were hampered by insufficient reporting methods of randomization and allocation concealment, improper blinding, and inadequate strength of the inference. To date, no appropriately powered randomized controlled trials (RCTs) of AA for sciatic pain associated with a herniated lumbar disc have been conducted.

Time-dependent characteristics of acupuncture might be one of the most important factors in the assessment of its effects in the relief of pain. Based on the time-dependent characteristics of acupuncture, the effects of acupuncture are generally classified as either immediate (after the end of the first treatment session) or cumulative (after repeated acupuncture stimulation).^[23,24]^ So far, most clinical trials and systematic reviews assessing the role of acupuncture have focused on the cumulative effects of repeated acupuncture stimulation. However, the immediate effects could have clinical significance and methodological advantages. Immediate pain reduction might motivate the patient to continue treatment and facilitate further physiotherapy. Patients who receive little benefit or no immediate analgesic effect following the first treatment might be expected to be less likely to gain benefit from repeated stimulation. Notably, for many patients with acute pain such as that resulting from surgery or childbirth, the reported analgesic effects of acupuncture are usually immediate. Furthermore, the results of some functional magnetic resonance imaging (fMRI) studies have suggested that the immediate and cumulative effects of acupuncture treatment elicit different temporal neural responses in a wide range of brain networks,^[25,26]^ which could explain the underlying specific mechanisms of the immediate effects of acupuncture.

Therefore, we propose an RCT to evaluate the immediate effect of AA for sciatic pain associated with a herniated lumbar disc. The results of our clinical trial might guide better rational and selective use of acupuncture as a treatment for sciatica in the future.

## Methods

2

### Trial design

2.1

The study is designed to be a randomized, three-arm, parallel-group, controlled trial to evaluate the immediate efficacy, safety, and acceptability of AA therapy for sciatic pain due to a herniated lumbar disc. The three arms are AA, sham AA, and traditional needle manipulation (TNM). The clinical trial is patient/assessor-blinded, thus adhering strictly to SPIRIT (Standard Protocol Items for Randomized Trials) guidelines.^[27]^ The flowchart of the study protocol is shown in Figure 1 and the trial schedule is shown in Figure 2.

**Figure 1 F1:**
[figure not shown]
Participant flow diagram.

**Figure 2 F2:**
[figure not shown]
The trial schedule. AAPR. AAPR = Abbreviated Acceptability Rating Profile.

### Ethics and registration

2.2

The study protocol (version 3.0, informed consent form included) is in line with the Declaration of Helsinki and has been approved by the Institutional Review Board (IRB) of Shanghai Yueyang Hospital affiliated to Shanghai University of Traditional Chinese Medicine (reference: 201517). This trial has been registered with the Chinese Clinical Trial Registry (ChiCTR-IPR-15007127, URL: http://www.chictr.org.cn/showprojen.aspx?proj=11989). Before randomization, all patients will be requested to sign a written informed consent, and they will be absolutely free to choose whether or not to continue the trial at any time.

## Participants

3

### Inclusion criteria

3.1

Patients will be included if they meet all of the following criteria: (1) age between 18 and 55 years (either sex); (2) primary complaint of unilateral leg pain radiating below the knee; (3) ipsilateral lumbar disc herniation at the corresponding level verified by MRI or computed tomography^[28]^; (4) duration of pain < 5 years; (5) pain intensity score of 40 mm or more on a 100-mm visual analog scale (VAS); (6) willingness and ability to accept needle-acupuncture intervention and to comply with the requirements of the study protocol; and (7) signed informed consent.

### Exclusion criteria

3.2

Patients with any of the following conditions will be excluded: (1) leg pain originating from the upper lumbar column (L1–L3); (2) history of spine trauma or spine surgery; (3) history of stroke, heart diseases or severe hypertension, any endocrine diseases such as hyperthyroidism, and severe infection; and (4) other therapies, especially analgesics, in the past 7 days.

### Recruitment and screening procedures

3.3

Patients will be recruited at Shanghai Yueyang Hospital affiliated to Shanghai University of Traditional Chinese Medicine, with a target sample size of 90 subjects. Two strategies will be adopted to recruit participants with sciatica. One is to recruit participants in outpatient clinics. The other is to share electronic posters (containing brief introductions about the population needed, the free acupuncture treatment offered to eligible participants, and the contact information of the researcher) via the Internet.

The initial phone screening, which will involve recording the age and course of low back pain will determine potential eligibility, and then screening forms will be completed by interested participants via a face-to-face interview (diagnosis by a physician and assessment by a researcher) at the hospital sites. Only those interested participants who meet the eligibility criteria will be scheduled to sign written informed consent.

### Randomization/allocation

3.4

Only those participants who have signed informed consent and go through the screening will be assigned randomly to one of the three interventions in a ratio of 1:1:1. Randomization number will be generated using a computerized number generator through the stratified block randomization method of the Statistical Analysis System (SAS) package (V.9.1.3; SAS Institute Inc., Cary, North Carolina) by a researcher not involved in this trial. The random numbers will be stored in sealed envelopes for random allocation until an investigator opens each envelope closely before intervention.

### Blinding

3.5

AA inserts needles into the subcutaneous tissue with no needle-manipulation sensation; sham AA is non-penetrating with a slight prick on the skin; and TNM involves penetration with no needle manipulation. Therefore, it is possible to blind the patients to the treatment. All participants will be told that they will receive an innovative type of acupuncture and that they may not feel any sensation characteristic of traditional acupuncture except for minor pain caused by puncturing through the skin. The participants will be treated separately using the same equipment (disposable sterile steel needles retained for a total of 20 minutes, 75% alcohol to disinfect the skin) and instructed during intervention without any implying words. Outcome assessors and data analysts will be masked to the intervention allocation throughout the study.^[29]^ Although acupuncturists will not be blinded to group allocation, they will not be involved in the outcome assessments or data analyses.

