## Interventions

4

The patients will be guided to lay supine on a couch with their affected leg exposed. As shown in Figure 3A, the needling point will be at the ankle zone 5 of the affected leg. This point is located three fingers above the lateral malleolus and posterior margin.^[19]^

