### AA group

4.1

After sterilizing with 75% ethanol at and around the needling point, a disposable sterile acupuncture needle (0.35 mm × 40 mm; Tianxie Brand, Beijing, China) will be used. The acupuncturist will hold the needle and swiftly insert it into the skin at the target point with a 30° angle to the skin. Then, the needle will be slowly advanced with a 0° angle to the skin until about 3/4 of the needle enters the subcutaneous tissue. The patients will not feel any *deqi* during this process if the AA is performed correctly. Then, the needle will be retained in the subcutaneous tissue for 20 minutes with the needle handle fixed to the skin with an adhesive tape (Fig. 3B and C).

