### Sham AA group

4.2

A disposable sterile acupuncture needle (0.35 mm × 13 mm; Tianxie Brand) will be blunted before intervention so that it cannot be inserted into the skin easily. The skin will be sterilized as in the AA group. The acupuncturist will hold the blunt needle and prick the skin for 3 seconds, after which the needle will be pushed down to the skin. The needle will be retained for 20 minutes with the needle handle fixed to the skin with an adhesive tape.

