### TNM group

4.3

After sterilizing with 75% ethanol, a disposable sterile acupuncture needle (0.35 mm × 13 mm; Tianxie Brand) will be used. The acupuncturist will hold the needle perpendicularly to the skin and swiftly insert to a depth of 2–3 cm into the skin at the target point. Then, the needle will be retained for 20 minutes without any movement (Fig. 3D).

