In this study, we will focus on the immediate effect of AA on sciatic pain associated with a herniated lumbar disc. The measurements will only be conducted for a single session of AA treatment. There are many methodological advantages. For example, natural remission of disease, regression to the mean in clinical studies, and other factors disturbing the internal validity of results should play a minor role compared with other study designs.^[38,39]^ However, it is notable that a single treatment is not adequate in patients suffering from chronic pain. From a clinical point of view, the cumulative effect of acupuncture has been considered as an important factor associated with its clinical efficacy.^[40]^ Given that cumulative effects of repeated acupuncture are not simply because of overlapping immediate analgesic effects,^[41,42]^ further rigorous, high-quality, RCTs comparing acupuncture with no treatment and sham acupuncture are required to evaluate the cumulative effects of repeated AA stimulation.

A major limitation of the present study is that the acupuncturist will not be blinded to the treatment. However, the patients will be blinded to the acupuncture treatments since they cannot distinguish true from sham AA. In addition, the treatment duration will be similar in the 3 groups, and pain will be evaluated by a clinician who is unaware of the treatment received, at a time when all needles have been withdrawn. In addition, the use of an appropriate control group is a critical issue in designing a high-quality clinical trial. It is difficult to provide scientifically robust sham treatments as controls because the specific mechanisms and causal pathways of AA are not known. For example, it is unknown whether there are neural pathways associated with both specific and nonspecific effects, such as those associated with self-healing. In this study, we set 2 control groups. In the sham AA group, the needle tip just pricks on the skin without penetrating. In the TNM group, the needle tip will be swiftly inserted into the skin at the target point at a 90-degree angle. Therefore, 2 control groups set in this study will prove the specificity of AA in the treatment of sciatic pain associated with a herniated lumbar disc.

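### The patient-blinding argument covers sensation and information but not sight: the arms differ in needle length, tip, angle and stated fixation on an exposed leg, chiefly TNM against the other two

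*Protocol article*

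**What the plan says.** Section 3.5 (Blinding) describes the sensation expected in each of the three arms and concludes: "Therefore, it is possible to blind the patients to the treatment". Three supports follow. The first is common information: "All participants will be told that they will receive an innovative type of acupuncture", with a warning that the usual acupuncture sensation may be absent apart from minor pain as the skin is punctured. The second is neutral wording during treatment. The third is: "The participants will be treated separately using the same equipment", with a bracket that lists disposable steel needles, 20 minutes' retention and 75% alcohol.

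Section 4 (Interventions) sets the scene: "The patients will be guided to lay supine on a couch with their affected leg exposed". The arms are then described separately:

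- **AA (4.1):** a 0.35 × 40 mm needle enters at 30°, then advances at 0° until about three quarters is under the skin; "the needle will be retained in the subcutaneous tissue for 20 minutes with the needle handle fixed to the skin with an adhesive tape".
- **Sham (4.2):** a 0.35 × 13 mm needle "will be blunted before intervention so that it cannot be inserted into the skin easily". It pricks the skin for 3 seconds, is pushed down to the skin, and its handle is taped.
- **TNM (4.3):** a 0.35 × 13 mm needle is inserted perpendicularly to a stated depth of 2–3 cm; "the needle will be retained for 20 minutes without any movement". No tape is mentioned.

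The Discussion returns to blinding: "the patients will be blinded to the acupuncture treatments since they cannot distinguish true from sham AA". Section 5.1 makes the pain VAS at 0 minutes after treatment the primary endpoint, marked by the patient. The Abstract says that the success of blinding will be evaluated.

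**The concern.** The stated argument for patient blinding deals with what the patient feels and is told. It does not deal with what the patient may see during 20 minutes on a couch with the leg uncovered. By the article's own description, an AA needle lies flat under tape while a TNM needle stands upright, apparently without tape.

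Blinded assessors and analysts do not protect a pain score that the patient marks. If the appearance of the needle changes what the patient expects, and does so differently by arm, the difference enters the 0-minute VAS and cannot be separated from a treatment effect. The Discussion relies on both control groups to establish that AA is specific, so each contrast needs its own protection. The Discussion's statement on indistinguishability addresses only true against sham AA.

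**Working it through.** The plan gives no figure on this point, so the check is mainly a comparison of its sections.

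**Step 1. What is common and what differs (sections 3.5 and 4.1–4.3).**

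| Feature | AA | Sham | TNM |
|---|---|---|---|
| Needle | 0.35 × 40 mm | 0.35 × 13 mm, blunted | 0.35 × 13 mm |
| Skin penetrated | yes | no | yes |
| Position | 30°, then 0° | pushed down to the skin | perpendicular |
| Handle taped | yes | yes | not stated |
| Retention | 20 min | 20 min | 20 min |

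The bracket in 3.5 fits the retention row, the use of disposable needles and the skin preparation. Length, tip, angle and fixation lie outside it.

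**Step 2. Pair by pair.**

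- *AA vs TNM:* length, angle and stated fixation all differ.
- *Sham vs TNM:* same nominal size; tip, penetration, angle and stated fixation differ.
- *AA vs sham:* length, tip and penetration differ, but both are taped and both appear to lie along the skin (for sham this is my reading of the text).

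**Step 3. What remains outside the skin during retention**, taking the stated lengths as shaft lengths (an assumption).

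- AA: 40 mm × (1 − 3/4) = 10 mm.
- Sham: 13 mm, since nothing penetrates.
- TNM: cannot be derived. A 13 mm shaft is 20 − 13 = 7 mm to 30 − 13 = 17 mm shorter than the stated depth of 2–3 cm, so section 4.3 contradicts itself.

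About 10 mm against 13 mm, both under tape, is a weak cue. AA and sham are therefore best told apart at insertion, and the clearest cue during retention is TNM against the other two.

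**Step 4. How much a given bias would matter (illustration only).** The documents give no SD and no basis for the size of an expectation effect, so both are assumed. With 26 evaluable patients per arm (section 6.1), a two-sided 5% test, a normal approximation and no true effect:

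- SE of an arm difference = SD × √(2/26), which is 4.2, 5.5 and 6.9 mm for SD 15, 20 and 25 mm.
- False-positive rate = Φ(b/SE − 1.96) + Φ(−b/SE − 1.96) for a bias b.

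| Assumed bias | SD 15 | SD 20 | SD 25 |
|---|---|---|---|
| 3 mm | 11% | 8% | 7% |
| 5 mm | 23% | 15% | 11% |
| 10 mm | 67% | 44% | 30% |

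The table shows how sensitive one pairwise comparison would be. It is not an estimate of what will happen.

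**The case against.** There is a good deal to be said for the plan, and several stronger readings fail.

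- *That blinding rests on identical equipment, and that sections 4.1–4.3 flatly refute it.* A reader might infer this from the equipment sentence alone. The bracket limits that sentence to needle type, retention time and antiseptic, and the conclusion that blinding is possible comes before it, drawn from sensation. The wording is loose and could mislead, but it does not claim equal length, angle or fixation.
- *That all three arms look different throughout.* They do not: sham and TNM share a nominal needle size, AA and sham share the tape, and the exposed shafts of AA and sham are similar.
- *That patients will be unblinded.* This is not shown. The point lies above and behind the outer ankle of a supine patient, Figure 3 is not available here, and the full protocol may specify a screen that the article omits. Patients are treated separately, cannot compare arms, and are told that the technique is new. Seeing a needle does not by itself reveal which arm is the test treatment.
- *That the TNM argument is missing altogether.* Section 3.5 does name TNM in its reasoning on sensation; only the Discussion confines itself to true and sham AA.

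What remains is narrower. The article lists its blinding measures and none concerns sight. Prior experience of acupuncture is not an exclusion in section 3.2, so some patients may recognise an upright needle as conventional. The planned check of blinding can detect a failure but cannot prevent one.

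**Conclusion.** The point holds in limited form, as an inexpensive improvement. The arms are described as differing in features that a patient could see, the blinding argument does not address sight, and the primary outcome is marked by the patient straight after treatment. Expectation could therefore bias the contrasts meant to show specificity, mainly AA versus TNM; for AA versus sham the exposure is mostly at insertion.

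This rests on two assumptions: that patients can see the point, and that no screen is specified in the full protocol. The size of any bias cannot be derived from the documents. A reader might take the illustrative rates above as a forecast, but nothing in the article supports a particular value. Two matters need reconciling whether or not a screen exists: the equipment wording, and the TNM needle length against its stated depth. If the length is what changes, the match in nominal size between sham and TNM would also have to be looked at again.

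**What to change.** In section 3.5:

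1. Screen the ankle from the patient's view in the same way in all three arms, from before needling until after the 0-minute VAS has been marked. If the full protocol already provides this, one sentence in the article is enough.
2. Reword the equipment sentence to name what is common and to say that needle length, angle and fixation differ.
3. State the blinding argument separately for AA vs sham, AA vs TNM and sham vs TNM. A screen removes sight but not touch, so the argument from sensation is still needed.

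In sections 4.1–4.3, reconcile the needle and fixation descriptions, including whether TNM needles are taped and how a 13 mm needle fits a depth of 2–3 cm. Which figure is right is for the investigators to settle.

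The cost is a screen and a little set-up time, with no extra patients. I would not tie this to asking for the treatment guess directly after the 0-minute VAS: that could prime the later ratings (15 and 30 minutes, 2 hours, days 3 and 7), so its timing is a separate trade-off.
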